### Study procedures

Eligible patients will be identified by the local multidisciplinary staff among patients with an indication of brain irradiation following the diagnosis of benign meningioma or atypical meningioma. The decision of radiotherapy should be made by the local multidisciplinary committee of each investigator center. Once checked all eligibility criteria, the radiation oncologist will propose the study to patients. Patients will be given study information (explanation on the study, reading and giving of the information notice). Patients will have a reflection period of the duration of their choice.

The specific exams/procedure requested in the study before inclusion (baseline visit) will be performed after consent signature and before inclusion. Inclusion will be thus performed.

The choice of the irradiation modality is at the discretion of the radiation oncologist: hypo-fractionated stereotactic radiotherapy (SRT), normo-fractionated intensity-modulated radiotherapy (IMRT), or proton-therapy (PRT) according to each center routine.

For enrolled patients, within 6 weeks before inititation of brain irradiation, the following evaluations will be performed in the investigator center. Procedures are summed up in Table 2.

**Table 2 Tab2:** Study procedures

	Screening before inclusion	Baseline assessment (within 6 weeks before radiotherapy start)	During radiotherapy period (7 weeks) for 3 cohorts: - Cohort IMRT - Cohort SRT - Cohort PRT	End of radiotherapy	AFTER THE END of radiotherapy	
					6 and 12 months	Yearly up to 10 years
Study explanation and signed informed consent before any study procedures	✓					
**Patients**						
**Standard physical and neurological examination (Nano-scale)**		✓	✓ Weekly during radiotherapy		✓	✓
**Cognitive assessment** (by a trained neuropsychologist): - *Executive functions* - *Episodic memory* - *Working memory* - *Short-term memory* - *Attention/Information processing speed* - *Prospective memory (Mem-Pro* Clinic)		✓			✓	✓ **(at 3**,** 5**,** 7 and 10 years only)**
**Brain MRI** (standard follow-up):3DT1w, Diffusion (b = 0 and b = 1000 s.mm-2, 30 directions), Perfusion (Dynamic Susceptibility Contrast, DSC-MRI), 3DT1 Gadolinium, 3D Fluid Attenuated Inversion Recovery (FLAIR), Angiographic “time of flight” sequence (TOF)		✓			✓	✓
**Cognitive complaints**,** anxiety and depression assessment** *Fact-Cog* *- HADS* *MFI*		✓			✓	✓
**Quality-of-life assessment** *- EORTC QLQC30 + BN20*		✓			✓	✓
**Evaluation of the socio-professional** **reintegration**		✓			✓	✓
*At the discretion of the investigator*: Endocrinological, ophthalmological and audiometric evaluations		✓			✓ (12 months only)	✓
	*OPTIONAL*					
Blood sample banking		✓		✓	✓	✓
Participants free of brain disease						
	Baseline assessment (within 6 weeks before radiotherapy start)	6 and 12 months	Yearly up to 10 years			
**Cognitive assessment** (by a trained neuropsychologist): - *MoCA* - *Executive functions* - *Episodic memory* - *Working memory* - *Short-term memory* - *Attention/Information processing speed* - *Prospective memory (Mem-Pro* Clinic)	✓	✓	✓ **(at 3**,** 5**,** 7 and 10 years only)**			
**Cognitive complaints**,** anxiety and depression assessment** *Fact-Cog* - *HADS* - *MFI*	✓	✓	✓			
**Quality-of-life assessment** - *EORTC QLQC30*	✓	✓	✓			

#### Irradiation

Radiotherapy will be initiated within 6 weeks after inclusion and will last 7 weeks at maximum.

The localization of radiotherapy treatment will depend on the decided radiotherapy modality:

Patients in the IMRT and SRT cohorts will thus be treated in the investigator center.Patients in the PRT cohort will be addressed by the investigator, as usual in case of treatment by proton-therapy, to the the site of proton therapy of Caen. The dosimetry and the pretreatment imagery will be performed by the proton therapy center.

All patients will have to complete the brain irradiation schedule in less than 45 days, from the first day of irradiation to the last day. Treatment should not be protracted over more than 45 days. Delineation should be performed on a 1-millimeter scanner and patients should be immobilized with a thermoplastic mask. Baseline MRI should be registered with the dosimetric scan to allow an accurate delineation of the target and organs at risks (OAR).

For grade I meningioma, prescription dose will be 50-54GyRBE (1,8–2 Gy per fraction) for IMRT and PRT cohorts or 25 Gy (5 Gy per fraction) (D2% between 125 and 140%) for SRT cohort.

For grade II meningioma, prescription dose will be 54-60GyRBE (1,8–2 Gy per fraction) for IMRT and PRT cohorts. SRT is not allowed.

Details about OAR delineations and dosimetric dose constraints are given in the Supplementary material n°1.

#### Follow up after irradiation

Evaluations will be realized **at 6 months**,** 1 year and every year until 10 years after the end of radiotherapy (**Table 2). Cognitive assessment will be performed only at 6 months, 1 year, 3 years, 5 years, 7 years and 10 years.

#### Patient withdrawal

The participation to the study will be interrupted at any time under the following circumstances:

Patient request (data already collected during the study will be stored and used unless the patient expresses his/her opposition, withdrawal of consent for further treatment).Patient may stop to participate to the study at any time, on his/her request, without any requirement to justify the study withdrawal. The withdrawal may be given orally or in writing. However, the investigator is responsible to take note of reason for study withdrawal, without question the patient’s wish, and has to document it, as well as the date of withdrawal.Concomitant disease or other reason requiring the discontinuation of study participation.Investigator’s request (with detailed documentation of reasoning).Non-compliance of patient.patient lost to follow-up.Trial termination by the sponsor.Death.

Any patient who prematurely withdraws from the study treatment only will continue to be followed, unless she withdraws from the study.

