### Statistical design overview

The primary endpoint is the proportion of patients with an impairment in cognitive parameters 10 years after irradiation of skull base benign meningioma, or atypical meningioma.

As there are no available data in the literature concerning the prevalence of long-term cognitive disorders after radiotherapy treatment of skull base benign meningioma, or atypical meningioma, we assume that approximately 50% of patients will present an impairment of their cognitive functions 10 years after the end of irradiation. Using a 95% confidence interval with a width of 0.2 for a small sample size, a total of 93 patients is required.

In order to document the impact of brain irradiation on cognitive performances for each of the 3 radiotherapy modalities usually used in this indication, 31 patients are required in each of the 3 cohorts (IMRT, SRT, PRT).

In addition, a control group with 31 assessable participants free of brain disease will be constituted.

In order to anticipate 15% of subjects possibly non assessable, 36 subjects per each of the 4 cohorts will be enrolled, for a total of 108 patients and 36 participants free of brain disease.

Categorical variables will be summarized using numbers and proportions. Quantitative variables will be summarized using quartiles and range (mean and standard deviation for Gaussian-like variables). The pattern of missing data will be described.

Briefly, all outcomes will be analyzed based on intention-to-treat principle. For each cohort, the Intention to Treat (ITT) population is defined as all patients included in this radiation arm, regardless of whether eligibility criteria are met and whether or not radiation therapy is used.

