#### Primary objective

The proportion of patients with an impairment in cognitive parameters 10 years after irradiation of skull base grade I-II meningioma will be estimated with a 95% confidence interval in each cohort.

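### The withdrawal rule ends follow-up, and with it the 10-year cognitive test, for non-compliance and some concomitant disease; this risks outcome-related loss and conflicts with the intention-to-treat analysis

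*Protocol article*

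**What the plan says.** All references are to the protocol article.

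- **Patient withdrawal** opens with "The participation to the study will be interrupted at any time under the following circumstances". What ends is participation in the study, not only treatment. The listed reasons include "Non-compliance of patient" and "Concomitant disease or other reason requiring the discontinuation of study participation", besides patient request, investigator's request, loss to follow-up, sponsor termination and death.
- The same section promises continued follow-up only to patients who stop the study treatment and nothing else. It says that data already collected are kept and used, but only under the patient-request item.
- **Irradiation** limits radiotherapy to 7 weeks. **Follow up after irradiation** sets cognitive tests at 6 months and at 1, 3, 5, 7 and 10 years.
- **Statistical design overview**: "The primary endpoint is the proportion of patients with an impairment in cognitive parameters 10 years after irradiation". It also says that "all outcomes will be analyzed based on intention-to-treat principle", with the population defined as all patients included in the radiation arm. On missing data it says "The pattern of missing data will be described".
- **Primary objective**: the proportion "will be estimated with a 95% confidence interval in each cohort". No rule is given for counting a patient without a 10-year test.

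**The concern.** In a 10-year study of cognition, missed visits and unfinished tests are a plausible consequence of the outcome being measured. The article itself points that way. The Eligibility criteria admit only patients whose neuropsychological abilities let them follow the protocol, so the link between cognition and compliance is recognised at entry. The Background says that cognitive problems after radiotherapy can sometimes progress to dementia. It also reports a pilot study in which brain ageing appeared to accelerate with time since radiotherapy.

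A patient who declines at year 6 and becomes an irregular attender can, under the rule as written, be taken out of the study before the 10-year test. The clause on continued follow-up does not help, because treatment ended years before. If such patients go missing more often than others, the 10-year proportion may understate the harm that the study was set up to measure. The Discussion expects the results to guide the choice of irradiation technique. An analysis plan can impute or bound a missing score, but it cannot recover a test that was never done.

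**Working it through.** **1. The passages side by side.** Intention to treat, as defined in the Statistical design overview, needs a 10-year outcome, or at least an attempt to obtain one, for every included patient. The Patient withdrawal section stops outcome collection in some patients who have not withdrawn consent. Both cannot be carried out in full. The only safeguard applies to stopping a treatment of at most 7 weeks, so for nearly all of the 10 years it has almost no one to protect.

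**2. The plan's own figures.** The sample size rests on this statement: "we assume that approximately 50% of patients will present an impairment of their cognitive functions 10 years after the end of irradiation". With a 95% interval of total width w = 0.2, the Wilson interval at p = 0.5 needs n = (1.96/0.2)² − 1.96² = 96.04 − 3.84 = 92.2, so 93. This is the stated total, or 31 per cohort. With 15% not assessable, 36 enrolled leave 36 × 0.85 = 30.6, about 31.

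**3. Illustration of informative loss.** The inputs from the plan are p = 0.50 and overall loss L = 0.15. The assumptions are:

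- only patients tested at 10 years are counted;
- impaired patients are lost RR times as often as unimpaired patients.

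Then:

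- loss in the unimpaired: l0 = 2L/(1 + RR)
- loss in the impaired: l1 = RR × l0
- reported proportion: 0.5 × (1 − l1)/(1 − L)

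| L | RR | l0 | l1 | Reported |
|---|---|---|---|---|
| 0.15 | 1 | 0.150 | 0.150 | 0.50 |
| 0.15 | 2 | 0.100 | 0.200 | 0.5 × 0.800/0.85 = 0.47 |
| 0.15 | 3 | 0.075 | 0.225 | 0.5 × 0.775/0.85 = 0.46 |
| 0.15 | all lost are impaired | 0 | 0.300 | 0.5 × 0.700/0.85 = 0.41 |
| 0.30 (assumed) | 2 | 0.200 | 0.400 | 0.5 × 0.600/0.70 = 0.43 |
| 0.30 (assumed) | 3 | 0.150 | 0.450 | 0.5 × 0.550/0.70 = 0.39 |

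For scale, the Wilson half-width at p = 0.5 is about 10 points for 93 patients and about 17 points for one cohort of 31.

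**4. The share due to these clauses.** The table treats the whole loss as outcome-related. The 15% is not broken down by reason. Suppose a share f of it is outcome-related and the rest is unrelated. The shift is then 0.5 × f × L × (RR − 1)/(RR + 1)/(1 − L). At L = 0.15:

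- f = 1: 0.5 × 0.05/0.85 = 2.9 points for RR = 2, and 0.5 × 0.075/0.85 = 4.4 points for RR = 3.
- f = 1/2 (assumed): 1.5 and 2.2 points.

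**5. Dependence on the counting rule.** Take one cohort of 36 with 18 truly impaired and, at the extreme, 5 lost patients who are all impaired. The result is 13/31 = 0.42 among those tested, 13/36 = 0.36 if missing counts as unimpaired, and 18/36 = 0.50 if missing counts as impaired. The direction of any error therefore depends on a rule that the article does not state.

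**The case against.** A reader might infer that the primary proportion is computed only on patients still assessable at 10 years and is therefore biased downwards. The documents do not support that reading. The word assessable appears in the sample-size text; the analysis population is all included patients. Counting missing patients as impaired would give no downward bias, and withdrawals unrelated to cognition would not shift the result. The documents give no figure linking decline to withdrawal.

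Four further objections have weight.

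- This is a condensed article. A rule for missing 10-year scores, including any use of earlier visits, may be in the full protocol or the analysis plan. Its absence here is not an error.
- The concomitant-disease item applies only where the disease requires the patient to leave the study. Some of those patients could not be tested whatever the wording.
- Non-compliance is not defined. Reading it as missed visits or tests is an interpretation, though a natural one.
- Some patients who decline will be recorded as lost to follow-up, and no change to these two clauses would keep them. Decline seen before withdrawal can still inform secondary outcomes such as the delay to deterioration.

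These objections remove any claim of proven bias and any precise size. They do not remove the text itself: participation ends for non-compliance, the safeguard is nearly empty after radiotherapy, and an unseen analysis plan cannot replace tests that were not done.

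**Conclusion.** The point holds in a limited form. The withdrawal rule ends 10-year outcome collection for reasons that may follow from cognitive decline, and it conflicts with the intention-to-treat statement. It risks informative loss and an underestimated 10-year proportion, but it is not shown to cause either.

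If only assessable patients were analysed, a true 50% would be reported as about 46% to 47% at the planned 15% loss with impaired patients lost two to three times as often, and as 41% at the extreme. The loss ratios, the complete-case analysis and the 30% scenario are assumptions, and only an unknown part of any such shift would come from these two clauses. This is a worthwhile, inexpensive improvement and not a flaw that undermines the study.

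**What to change.** Amend the Patient withdrawal section so that neither non-compliance, nor concomitant disease in a patient who still consents and can be tested, ends follow-up. State that such patients are still invited to every remaining cognitive visit, including year 10. The other listed reasons need not change for this purpose. The amendment concerns data collection only and alters no treatment.

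The cost is a short amendment and some extra effort to contact irregular attenders. Inclusions began in 2023, so the 10-year tests are still years away and the change can take effect before most of the possible loss.

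As a recommendation for the analysis plan, and not as an error found: impute missing 10-year scores from the earlier cognitive visits, and report best- and worst-case bounds alongside.

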## Discussion

Given the excellent prognosis of skull base meningioma, every effort should be done to avoid radiation induced long-term toxicities, particularly, neuro cognitive impairment. Modern technical of irradiation are widely used in this indication, and lead to a better protection of healthy tissue.

However the clinical proof level of these technical (IMRT, PRT, SRT), concerning any cognitive benefit, remains poor. Randomized trials are difficult to set up due to issues such as access to proton-therapy.facilities. CANCER COG results will be crucial to help radiation oncologists to choose the most appropriate irradiation technical.

First inclusions started on August 2023. Final results are expected between 2030 and 2035.

## Data Availability

No datasets were generated or analysed during the current study.

## Abbreviations

CPP: Ethics Committee (Committee for the Protection of Persons)
DSC: Dynamic Susceptibility Contrast
ECOG: Performance statut Eastern Cooperative Oncology Group performance status
EORTC: QLQC30 + BN20 European Organisation for Research and Treatment of Cancer quality of life questionnaires
FACT-Cog: Functional Assessment of Cancer Therapy Cognitive Scale
FLAIR: 3D Fluid Attenuated Inversion Recovery
Gy: Gray
HADS: Hospital Anxiety and Depression Scale
HVLT: Hopkins Verbal Learning Test
IMRT: Intensity-modulated radiotherapy
LNC: French League against Cancer
MFI: Multidimensional Fatigue Inventory
MoCA: Montreal Cognitive Assessment
MRI: Magnetic resonance imaging
NTCP: Normal tissue complication probability
OAR: Organs at risks
PFS: Progression-free survival
PRT: Proton-therapy
QoL: Quality of life
RANO: Response Assessment in Neuro-Oncology
RBE: Relative biological effectiveness
SRT: Stereotactic radiotherapy
TCP: Tumoral control probability
TOF: Angiographic “time of flight” sequence
VMAT: Volumetric arc therapy
WHO: World Health Organization
